## Abstract

**Background:**

The prevalence of heart failure (HF) is rising in industrialized and developing countries. Though invasive coronary angiography (ICA) remains the gold standard for anatomical assessment of coronary artery disease in HF patients, alternatives are being sought. Computed tomographic coronary angiography (CTA) has emerged as an accurate non-invasive diagnostic tool for coronary artery disease (CAD) and has been demonstrated to have prognostic value. Whether or not CTA can be used in HF patients is unknown. Acknowledging the aging population, the growing prevalence of HF and the increasing financial burden of healthcare, we need to identify non-invasive diagnostic tests that are available, safe, accurate and cost-effective.

**Methods/Design:**

The proposed study aims to provide insight into the efficacy of CTA in HF patients. A multicenter randomized controlled trial will enroll 250 HF patients requiring coronary anatomical definition. Enrolled patients will be randomized to either CTA or ICA (n = 125 per group) as the first test to define coronary anatomy. The primary outcomes will be collected to determine downstream resource utilization. Secondary outcomes will include the composite clinical events and major adverse cardiac events. In addition, the accuracy of CTA for detecting coronary anatomy and obstruction will be assessed in patients who subsequently undergo both CTA and ICA. It is expected that CTA will be a more cost-effective strategy for diagnosis: yielding similar outcomes with fewer procedural risks and improved resource utilization.

**Trial registration:**

ClinicalTrials.gov, NCT01283659

Team grant #CIF 99470

## Background

The prevalence of heart failure (HF) is on the rise in both industrialized and developing countries [1-3]. Though the diagnosis of HF often confers a poor prognosis, patient outcomes vary widely according to the underlying etiology of HF and subsequent therapy [2]. It has been long accepted that patients with ischemic cardiomyopathy and significant viable myocardium may derive mortality benefit from revascularization [2]. As such, invasive coronary angiography (ICA) is often recommended in patients with HF to define the presence or absence of coronary artery disease (CAD) as the inciting etiology.

ICA remains the gold standard for the anatomical assessment of coronary arteries and the diagnosis of luminal stenoses. However, access to ICA in Canada and other countries is limited, costly and has inherent risks (death (0.12%), myocardial infarction (<0.05%), stroke (0.1%) and bleeding (1.6%)), which prohibit its routine use in all patients. A non-invasive alternative to ICA would be desirable if it were available, accurate, safe, and cost-effective.

Computed tomographic coronary angiography (CTA) has emerged as an accurate non-invasive diagnostic tool for CAD [4-8] and has been demonstrated to have prognostic value [9-11]. Whether or not CTA can be used cost-effectively in HF patients for diagnosis and to guide patient investigations and management is unknown. This is the focus of this randomized controlled trial (RCT).

To date, there are limited randomized controlled trials (RCTs) that study the role of non-invasive imaging for the diagnosis and management of patients with HF [12]. To our knowledge, there are no RCTs examining the utility of CTA in HF patients. Acknowledging the aging population, the growing prevalence of HF and the increasing financial burden of healthcare [1-3], we need to identify non-invasive diagnostic tests that are cost-effective, readily available and safe, and of sufficient accuracy to risk stratify patients and guide investigations and management.

In 2007, the Canadian Institutes of Health Research New Frontiers Program consensus conference identified the need for comparative effectiveness research evaluation of imaging, particularly in HF. In response, the IMAGE-HF team project has been established The main goal of IMAGE-HF is to evaluate cardiac imaging in HF. Studies are divided into three broad levels: Level 1) research that compares the effective use of existing clinical practice strategies for HF to determine impact on relevant outcomes; Level 2) research to evaluate emerging methods to address specific HF populations; Level 3) research for the development and evaluation of novel imaging biomarkers in animal models of HF for potential translation to human studies. Level 1 projects comprise three independent trials: Project 1-A and 1-B are described separately [13,14]. The study herein is an IMAGE-HF Project 1-C called: *Computed Tomographic Coronary Angiography for Patients with Heart Failure (CTA-HF): A Randomized Controlled Trial.* This study will compare the resource utilization (downstream ICA, other testing and/or cardiac hospitalization) in terms of average health care costs per patient of CTA compared to ICA in patients with progressive or newly diagnosed HF (Figure 1).

**Figure 1 F1:**
[figure not shown]
**IMAGE-HF Project I-C: experimental algorithm to evaluate use of tomographic coronary angiography (CTA) in determination of heart failure (HF) etiology.** Figure 1 illustrates the experimental model of this study, in which the ability of CTA to determine etiology of HF will be compared to that of invasive coronary angiography (ICA). All patients exhibiting HF of unknown etiology will be considered; patients with contraindications to CTA will be excluded.

### Objectives

The primary objective of this RCT is to compare the average health care costs of CTA (experimental algorithm) to ICA (standard of care) (Figure 1) as the initial test for coronary anatomy in HF patients of unknown etiology. The secondary objectives are to compare CTA versus ICA for composite clinical events, major adverse cardiac events (MACE), quality of life (QoL), radiation exposure and safety.

### Hypotheses

The primary hypothesis is that, compared to ICA, a diagnostic strategy algorithm using CTA for HF patients will result in a reduction in downstream resource utilization leading to a reduction in average costs per patient.

The first of two secondary hypotheses states that compared to ICA (standard of care), a CTA strategy will achieve: a) similar composite clinical events (CCE) (cardiac death, myocardial infarction (MI), resuscitated cardiac arrest and cardiac re-hospitalization (worsening heart failure, acute coronary syndrome arrhythmia), QoL, and MACE (cardiac death, non-fatal MI); b) a lower rate of procedure related complications (death, MI, stroke, vascular complications, severe allergic reactions; contrast nephropathy); and c) a lower rate of normal ICA. The second of the two secondary hypotheses states that using patient-based analysis and vessel-based analysis, CTA has very good agreement with ICA among patients with HF in the CTA arm who proceed to ICA.

## Methods/Design

### Design

CTA-HF is a multicenter, multinational, randomized controlled trial that is currently recruiting 250 patients from 15 sites across Canada and Finland (see Additional file 1) over 4 years, randomized to CTA versus ICA (n = 125 per group) as the first test to define coronary anatomy in patients with heart failure. This research study has approval from each participating center’s institutional research ethics board.

### Eligibility criteria

All HF patients requiring investigation to determine the etiology of HF (ischemic versus non-ischemic) will be screened for the study. Eligible patients will have a documented history of left ventricular dysfunction (LVEF <50% by radionuclide angiography (RNA), echocardiography or magnetic resonance imaging (MRI)), or New York Heart Association (NYHA) Class II to IV symptoms, or an admission to hospital or emergency room for heart failure within the past 12 months. As well, the HF patient requires diagnostic information on coronary anatomy because the diagnosis of CAD is uncertain or the definition of coronary anatomy is required for management.

Patients will be excluded if they have: age <18 years, lack of consent, renal insufficiency (glomerular filtration rate, GFR <45 ml/min), allergy to intravenous contrast agents, contraindications to radiation exposure (for example, pregnancy), uncontrolled heart rate (HR, as per local clinical routine), history of revascularization, atrial fibrillation, frequent atrial or ventricular ectopy (>1/minute), inability to perform 20-second breath-hold, and CTA or ICA within the preceding 12 months.

### Randomization

Randomization will be coordinated by the University of Ottawa Heart Institute (UOHI) Cardiovascular Research Methods Centre. Eligible, consenting patients will be randomized to either the CTA or ICA arm and stratified according to recruitment site. A stratified block (varying sizes) randomization scheme will be used. Within each stratum, patients will be randomized with varying block sizes into the two study groups. A central randomization scheme, ensuring concealment, will be used and the site coordinator will perform patient assignments. The randomization scheme will be generated by the study statistician using a SAS (SAS Institute, Cary, North Carolina, USA) macro.

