### Secondary analysis

Secondary analysis will investigate CCE and MACE, analyzed using survival analysis techniques between the ICA and CTA arms. The survival experience (that is, time-to-major adverse cardiac event) in each of the two arms will be summarized using Kaplan-Meier product limit estimates and the log-rank test will be used for comparing the survival curves. The hazard ratio with 95% confidence interval (CI) will be calculated. To adjust for possible effects of covariates on survival, the Cox’s proportional hazards model will be used. Underlying assumptions for these statistical procedures will be assessed; in particular, the proportional hazard assumption will be assessed using graphical and numerical tests, and stratified Cox models or Aalen’s additive model will be considered as needed.

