#### Safety

The proportion of various procedural complications will be compared descriptively using chi-square tests to determine relative safety of CTA to ICA. Patient morbidity/health-related QOL associated with CTA and/or ICA will be compared using Student-t tests for the overall scores and utility.

The accuracy (operating characteristics) of CTA in the identification of high-risk coronary anatomy and obstructive CAD (per-patient/vessel/segment analysis) will be assessed in the cohort of patients undergoing both CTA and ICA. A receiver operating characteristic (ROC) curve analysis will be conducted for the vessel disease number, and the weighted kappa with 95% CI will be calculated to assess the agreement between CTA and ICA for the allocation of patients into the groups: 0-, 1-, 2- or 3-vessel disease; high-risk CAD; and non-high risk CAD. ROC analysis will also be performed on a per-patient, per-vessel and per-segment basis. In the patients who undergo both CTA and ICA, the accuracy of CTA to predict subsequent early revascularization will be assessed as follows: the point estimates with 95% CI for the sensitivity (S_e_), specificity (S_p_), positive predictive value (PPV), and negative predictive value (NPV) of CTA in identifying a patient for revascularization (medical therapy (no obstructive CAD) versus revascularization (PCI (non-high risk CAD) versus CABG (high-risk CAD)) using ICA as the gold standard will be calculated. They will be adjusted for referral bias using the Diamond method [18].

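### Randomisation is blocked within site, but the named tests for composite clinical events and quality of life ignore site, so they are mildly conservative if sites differ

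*Protocol article*

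**What the plan says.** All places are in the protocol article.

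- **Design:** the trial is "recruiting 250 patients from 15 sites across Canada and Finland", with 125 per arm.
- **Randomization:** eligible, consenting patients are "randomized to either the CTA or ICA arm and stratified according to recruitment site". Site is the only stratification factor. Blocks vary in size, and the sizes are not given.
- **Secondary analysis (CCE and MACE):** "the log-rank test will be used for comparing the survival curves", and "The hazard ratio with 95% confidence interval (CI) will be calculated". Neither sentence mentions site. A Cox model follows "To adjust for possible effects of covariates on survival", but the covariates are not named. Stratified Cox models appear only in the sentence on model checking: "the proportional hazard assumption will be assessed using graphical and numerical tests, and stratified Cox models" or an additive model are to be considered if needed. That makes them a remedy for non-proportional hazards, not a way to reflect the randomisation.
- **Safety:** procedural complications are compared descriptively with chi-square tests. QoL scores "will be compared using Student-t tests for the overall scores and utility".
- **Missing data:** continuous outcomes at several time points are to be handled by a repeated-measures mixed model (MMRM).
- **Costs associated with the use of CTA:** the primary outcome is analysed by a generalized linear model that controls for all potential covariates.

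**The concern.** Blocking within site balances the arms inside each site, so differences between sites largely cancel from the arm comparison. A test that ignores site still counts that variation as noise. Its standard error is then too large, its true size falls below 5%, and it loses power. For survival outcomes, an unstratified hazard ratio also lies closer to 1 than the within-site ratio whenever a real effect exists.

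Site differences are plausible here. CCE includes cardiac re-hospitalisation, which can depend on local admission practice; the sites lie in two countries; and heart-rate eligibility and CT acquisition follow local routine.

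Conservatism is not automatically the safe error. The hypothesis for CCE and QoL is that the two strategies give similar results. A test that rejects less often, with a hazard ratio nearer 1, leans towards that conclusion.

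**Working it through.** **The plan's own figures.** No size or power is stated for any secondary outcome, so there is nothing to reproduce on this point. The one sizing example concerns cost: with a coefficient of variation of 25%, a 10% reduction and 125 per arm, 0.10 / (0.25 × √(2/125)) = 3.16, and Φ(3.16 − 1.96) gives about 88.5% power at two-sided 5%. That agrees with the plan's claim of sufficient power and does not enter this point.

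**Inputs from the protocol.** 250 patients, 15 sites (250/15 ≈ 16.7 per site), 1:1 allocation in blocks within site, follow-up of 2 to 4 years.

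**Assumptions.** Two-sided 5% tests, unequal site sizes, blocks of 2 and 4, exponential event times, normally distributed site effects, CCE rates of 0.10 to 0.20 per year, and a true within-site hazard ratio of 1 (for size) or 0.60 (for power).

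**QoL, analytic.** With site-balanced arms, the true variance of the difference in means is (1 − ICC) times what the t-test assumes. Hence size = 2[1 − Φ(1.96/√(1 − ICC))]:

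- ICC 0.05: 1.96/√0.95 = 2.011, size 4.4%
- ICC 0.10: 1.96/√0.90 = 2.066, size 3.9%
- ICC 0.20: 1.96/√0.80 = 2.191, size 2.8%

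Simulation (5,000 runs) agrees: 4.3%, 3.9% and 3.0% without site, and 4.6 to 4.9% with site as a fixed effect. For a difference of 0.355 SD, power without and with site is 81.0% and 82.3% at ICC 0.05, and 80.3% and 82.8% at ICC 0.10.

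**CCE, simulated.** Each setting has 1,500 runs; the Monte Carlo standard error of a 5% size is √(0.05 × 0.95/1500) ≈ 0.6 points. Each cell gives unstratified / site-stratified.

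| Rate per year | Site log-hazard SD | Size, % | Power at HR 0.60, % | Estimated HR |
|---|---|---|---|---|
| 0.10 | 0 | 5.3 / 4.8 | 44.7 / 43.9 | 0.59 / 0.59 |
| 0.10 | 0.25 | 4.4 / 5.1 | 44.4 / 43.2 | 0.60 / 0.60 |
| 0.10 | 0.5 | 4.1 / 5.1 | 44.3 / 45.0 | 0.61 / 0.60 |
| 0.10 | 1.0 | 3.0 / 4.3 | 42.7 / 52.8 | 0.64 / 0.60 |
| 0.20 | 0 | 5.3 / 4.9 | 68.5 / 67.0 | 0.60 / 0.60 |
| 0.20 | 0.25 | 5.0 / 5.7 | 69.7 / 68.1 | 0.60 / 0.59 |
| 0.20 | 0.5 | 4.3 / 4.7 | 66.9 / 68.5 | 0.61 / 0.60 |
| 0.20 | 1.0 | 2.3 / 5.0 | 55.5 / 70.1 | 0.66 / 0.60 |

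At 0.15 per year (3,000 runs), size is 4.6 / 5.0% at SD 0.25, 4.7 / 5.1% at SD 0.5 and 2.9 / 5.0% at SD 0.8. Power is 58.4 / 57.1%, 57.9 / 59.7% and 54 / 61%.

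**What these SDs mean.** Sites one SD above and one SD below the mean differ in hazard by exp(2 × SD): 1.6-fold at SD 0.25, 2.7-fold at 0.5, 5.0-fold at 0.8 and 7.4-fold at 1.0.

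**Rare outcomes.** At an assumed MACE rate of 0.03 per year (about 21 to 28 events under the null) and SD 0.8, log-rank size is 4.3 / 4.8%, and power for a hazard ratio of 0.35 is 54.7 / 55.8%. For complications at 5%, chi-square size without site, against a Mantel-Haenszel test by site, is 4.8 / 4.6% at log-odds SD 0.5 and 4.8 / 5.2% at SD 1.0.

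**The case against.** The strongest reply is that this is a condensed article. Whether a log-rank test is stratified, and which covariates enter a Cox model, are details that an analysis plan often settles, and the open covariate list does not rule site out. That stands in part: a reader might infer that the plan excludes site from every secondary analysis, and the text does not say so. But the article does name its tests. A two-sample t-test cannot carry a site term, and stratified Cox is tied to another purpose. This is therefore a stated choice of method with a better alternative.

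Four further objections stand and limit the point:

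- The large effects need 5-fold to 7-fold differences in hazard between sites, and nothing in the protocol suggests such a spread. At SD 0.25 to 0.5 the power gap is about 1 to 2 points and can favour either test.
- A reader might call the unstratified hazard ratio biased. It is a marginal ratio and the stratified one is a within-site ratio. They are different quantities when an effect exists, and they coincide at 1, the value that similar event rates would imply.
- A reader might infer that the analysis favours a finding of similarity. The wider intervals also make harm harder to exclude, so the error cuts both ways. The lack of a margin for similarity is a separate matter.
- The t-test need not be the only QoL analysis. If QoL is measured repeatedly, the MMRM under Missing data can include site.

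**Conclusion.** The point holds for CCE and QoL as a minor one. The design blocks on site and the named tests do not use it, so they are conservative to the extent that sites differ. With moderate differences (log-hazard SD up to 0.5, ICC up to 0.10), size is roughly 4 to 5%, an HR of 0.60 moves by about 0.01, and power changes by no more than about 2.5 points. Only at SD 0.8 to 1.0 does the loss become material: size of 2.3 to 3.0%, and about 7 to 15 points of power. The site SDs, ICCs and event rates are all assumptions; the protocol gives none.

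Three wider readings are not supported. False-positive findings are not inflated; the error runs the other way. The chi-square comparison of complications needs no change: it is labelled descriptive, and the effect is negligible at a 5% rate, above the angiography risks quoted in the Background (at most 1.6%, for bleeding). The primary cost analysis is not affected as stated, because its regression model can carry site.

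**What to change.** - **CCE:** use a log-rank test and Cox model stratified by site. Pool very small sites within country, by a rule fixed before unblinding.
- **QoL:** replace the t-test with a linear model that includes site or, if QoL is measured repeatedly, include site in the MMRM already planned.
- **MACE:** if events are few, stratify by country or pooled sites. At 21 to 28 events, 15 sites would average only 1.4 to 1.9 events each.
- **Procedural complications:** leave the descriptive chi-square comparison as it is.

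The change is to analysis wording only. It needs no new data, since site is already used at randomisation. Its price is about one point of power if sites do not differ (0.8 to 1.5 points in the CCE simulations).

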### Data collection

All data will be collected using the Autonomy Process Automation (AMA) formally called Liquid Office™, which is a web-based solution for creating, routing, data capturing and managing electronic forms. This will be done in conjunction with the UOHI Cardiovascular Research and Methods Centre and will be audited using standard procedures.

Recruiting centers will be responsible for patient screening and local enrollment. Identification of patients will be coordinated by physicians and support staff responsible for scheduling coronary angiography. Local research staff (under direction from the site principal investigator) will identify and recruit patients for the study as well as be responsible for the day-to-day management of the study. A supervising research coordinator, based at the UOHI, will oversee the multicenter study at all sites and routine site visits will be made.

### Interventions

Patients will be randomized to CTA (experimental algorithm) versus ICA (standard of care).

#### Computed tomographic coronary angiography

Non-contrast enhanced prospective ECG-triggered image acquisition will be acquired and the Agatston score will be calculated [15]. Standard procedures will be applied for contrast infusion, timing and image acquisition. As per local clinical practice, prospective ECG-triggered or retrospective ECG-gated data sets will be acquired using bi- or tri-phasic contrast protocols. Vendor-specific radiation dose-reducing techniques such as prospective ECG-triggered image acquisition will be encouraged. A 4-point grading score [normal, mild (<50%), moderate (50 to 69%), severe (≥70%)] will be used for the evaluation of coronary stenosis using a 17-segment model. Similar to ICA, obstructive CAD is defined as coronary diameter stenosis ≥50% (Additional file 2).

#### Invasive coronary angiography

ICA will be performed according to standard clinical protocols, with selective coronary injection and images acquired from multiple oblique views (Additional file 2).

Patients with obstructive CAD will be categorized as having high risk CAD (defined as having a left main stenosis (≥50%), or three-vessel disease (VD) (≥70%) or two-VD (≥70%) involving the proximal left anterior descending artery) or non-high risk CAD [9].

Following either CTA or ICA, information on the results will be disseminated to the referring physician as part of their standard clinical care.

### Outcome measures

The primary outcome (average health care costs per patient) will be determined through regression methods detailed below.

All secondary outcome measures will be determined: (CCE (cardiac death, myocardial infarction, resuscitated cardiac arrest and cardiac re-hospitalization (worsening heart failure, acute coronary syndrome arrhythmia), QoL, procedural complications (all-cause death, myocardial infarction, stroke, vascular complications, severe allergic reactions; contrast nephropathy), and rate of normal ICA.

CTA accuracy: To address the 2^nd^ secondary hypothesis, regarding CTA accuracy, the accuracy in the cohort of patients randomized to CTA and undergoing subsequent ICA (sensitivity, specificity, predictive values and likelihood ratios) will be determined and reported with 95% confidence intervals (CI). It is estimated that 50/125 of the patients randomized to CTA will have subsequent ICA, which will enable the comparison of CTA accuracy to ICA.

### Frequency and duration of follow-up

Telephone follow-up will be performed at 3, 6 and 12 months, and every 12 months thereafter. Follow-up will continue until the termination of the trial (mean = 3 years; range 2 to 4 years) (Figure 2).

**Figure 2 F2:**
[figure not shown]
Timeline for IMAGE-HF Project I-C patient follow-up.

